#### Secondary outcome measures

Surgical outcomes (operative time, extracted myoma weight and number, required blood transfusion or not, switch to open surgery or not, postoperative drainage volume, length of postoperative hospital stays)Percent change from baseline in uterine fibroid size at the end of preoperative drug treatment (week 12)Percent change from baseline in uterine volume at the end of preoperative drug treatment (week 12) and post-surgical week 12Change from the predose value in hemoglobin at the end of preoperative drug treatment (week 12) and post-surgical day 1, week 4, and week 12Change from the predose value in menopausal-like symptoms: Kupperman Konenki Shogai Index (KKSI) at week 4, week 8, and week 12 of preoperative drug treatment and post-surgical week 4 and week 12Change from the predose value in disease-specific QOL: Uterine Fibroid Symptom Health-Related Quality of Life (UFS-QOL) at the end of preoperative drug treatment (week 12) and post-surgical week 12

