### Sample size {14}

The research hypothesis for this study is that when comparing the amount of intraoperative blood loss during LM after receiving either relugolix or leuprorelin for 12 weeks, the intraoperative blood loss for the relugolix group is no more than 50 mL greater than that for the leuprorelin group. Treatment success is defined according to the single-center pilot study that compared pre-treatment with leuprorelin versus no pre-treatment for intraoperative blood loss during LM. In the study, blood loss was 90.0 ± 67.4 mL [mean ± standard deviation (SD)] for pre-treatment with leuprorelin (*n* = 51) versus 148.2 ± 122 mL for no pre-treatment (*n* = 52) (not published). An increase in intraoperative blood loss not only delays postoperative recovery but also leads to a reduction in surgical quality. Based on our clinical experience, we considered a difference of 50 ml or less as acceptable and, therefore, used 50 mL as the non-inferiority margin. With a noninferiority margin of 50 mL, a mean difference of 0 mL, SD of 70 mL, a one-sided significance level of 2.5%, and power of 80%, the required number of subjects for analysis was calculated to be 64 (32/group). A dropout rate of 20% was assumed; thus, the number of participants was set at 80 (40 in each group).

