## Assignment of interventions: allocation

### Sequence generation {16a}

After the patients meet the study criteria and consent to participate, the investigator conducts screening tests and enters the patients’ data into the electronic data capture (EDC) system (SmartStage).

The EDC system determines eligibility based on input content and then randomizes the patients with the minimization method and 1:1 allocation. Adjustment factors are surgeon, the presence or absence of fibroids ≥ 9 cm in the largest dimension, and the presence or absence of the International Federation of Gynaecology and Obstetrics (FIGO) classification of fibroid types 1 to 5.

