## Data collection and management

### Plans for assessment and collection of outcomes {18a}

Investigators will collect data from study participants during nine visits: visit 1 for baseline data collection, visits 2 to 5 (12 weeks of treatment), visits 6 and 7 during hospitalization for surgery, and visits 8 and 9 (12 weeks of follow-up), for a study that will be completed in about 24 weeks. The planned schedule for data collection is shown in the “Participant timeline {13}” section.

Baseline, outcomes, and other trial collection and assessment data are directly recorded on the CRF. The investigator enters all data into the EDC system. The reliability and validity of the CRF are checked in the EDC system by EPS Corporation, the study’s contract research organization (CRO).

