## Statistical methods

### Statistical methods for primary and secondary outcomes {20a}

Summary statistics (number of patients, mean, SD, minimum, and maximum quartiles) and two-sided 95% confidence interval (CI) will be calculated for the primary outcome of interoperative blood loss for the full analysis set (FAS) or, if appropriate, the per-protocol set (PPS) for each treatment group. The FAS will include participants who received at least one dose of treatment after randomization and underwent LM with assessment of the primary outcome. The PPS will be the target population from the FAS, excluding trial participants who deviate from or violate inclusion criteria, take less than 80% of medications, or take prohibited concomitant medications.

Noninferiority of the test-drug group (relugolix) to the active-control group (leuprorelin) is demonstrated when the upper limit of the two-sided 95% CI for the difference in intraoperative blood loss between the groups is ≤ 50 mL. Student’s *t*-test will be used to conduct the noninferiority test with a margin of 50 mL and a one-sided significance level of 2.5%.

For secondary outcomes, categorical data will be used to calculate each category’s numbers and percentage for each treatment group’s analysis population. The Wilcoxon rank sum test will compare ordinal data, and items observed in the nominal category are compared between the two groups by the chi-square (*χ*^2^) test. Fisher’s exact test will be used for binary values. Continuous data will be summarized for each treatment group (number of patients, mean, SD, minimum, quartile, and maximum). In addition, summary statistics (sample size, mean, SD, minimum, quartile, and maximum) of the change from baseline (screening phase) for each visit will be calculated, and the two groups will be compared by Student’s *t*-test or Wilcoxon rank sum test.

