### Methods for additional analyses (e.g., subgroup analyses) {20b}

Subgroup analyses will not be conducted. However, when baseline factors differ between groups and might affect the primary outcome, an analysis of covariance (ANCOVA) with the factor as a covariate will be considered.

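### Continuous secondary outcomes are compared on change scores without the collected baseline as a covariate, which costs precision and leaves them open to chance baseline imbalance

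*Protocol article*

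**What the plan says.** The Secondary outcome measures section defines three outcomes as change from the predose value: hemoglobin (four time points), KKSI (five) and UFS-QOL (two). Two more are percent changes. One is "Percent change from baseline in uterine fibroid size at the end of preoperative drug treatment (week 12"); the other is uterine volume, at treatment week 12 and at post-surgical week 12.

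Statistical methods {20a} then fixes the comparison. Summary statistics "of the change from baseline (screening phase) for each visit will be calculated, and the two groups will be compared by" either a t-test or a Wilcoxon test. No covariate is named.

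Three other places bear on this:

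- Additional analyses {20b} says that "when baseline factors differ between groups and might affect the primary outcome, an analysis of covariance (ANCOVA) with the factor as a covariate will be" taken into consideration.
- Sequence generation {16a} lists the minimisation factors: "Adjustment factors are surgeon, the presence or absence of fibroids" of 9 cm or more, and the presence or absence of FIGO types 1 to 5.
- Plans for assessment {18a} names "visit 1 for baseline data collection", so the values needed for adjustment are collected.

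**The concern.** Subtracting the baseline does not remove its influence. Unless baseline and follow-up are almost perfectly correlated, change is negatively related to baseline. The arm that starts lower by chance then tends to show the larger rise, whatever the drug does. ANCOVA on the baseline value removes this and also reduces the residual variance.

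Nothing else in the article does that job. The ANCOVA in {20b} is tied to the primary outcome, depends on an imbalance being seen, and is only to be considered. Intraoperative blood loss has no baseline measurement, so that sentence does not reach the change outcomes. Minimisation partly limits imbalance in fibroid size, but does not directly balance hemoglobin, KKSI or UFS-QOL.

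At stake are secondary objectives 2 (fibroid size and uterine volume) and 3 (hemoglobin), and the menopausal-symptom and quality-of-life parts of 4. The sample size was set for blood loss alone, so precision on these outcomes is whatever 64 to 80 women provide.

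**Working it through.** **The plan's own figure.** Sample size {14} uses "With a noninferiority margin of 50 mL, a mean difference of 0 mL, SD of 70 mL" for the effect and its spread, and for the error rates "a one-sided significance level of 2.5%, and power of 80"%. It then states that "the required number of subjects for analysis was calculated to be 64 (32/group").

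- Normal approximation: n per arm = 2 × 70² × (1.960 + 0.842)² / 50² = 30.8, so 31.
- Noncentral t: power is 79.0% at 31 per arm and 80.3% at 32 per arm, so 32 per arm is reproduced.
- Dropout: 64 / (1 − 0.20) = 80, as stated.

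This calculation involves no change score, so the present point leaves it untouched. What carries forward is the planned evaluable size of 32 per arm.

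**Precision.** Let r be the correlation between baseline and follow-up and let both have SD σ. The document gives neither, so r is shown as a range and equal SDs are assumed. Per patient:

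- variance of the change score = 2σ²(1 − r)
- residual variance after ANCOVA on baseline = σ²(1 − r²)
- ratio, ANCOVA to change = (1 − r²) / [2(1 − r)] = (1 + r)/2

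| r | Change variance (σ²) | ANCOVA variance (σ²) | Ratio | Patients ANCOVA needs to match a change score with 64 | ANCOVA power where the change score has 80% |
|---|---|---|---|---|---|
| 0.3 | 1.40 | 0.91 | 0.65 | 41.6 | 94% |
| 0.5 | 1.00 | 0.75 | 0.75 | 48.0 | 90% |
| 0.7 | 0.60 | 0.51 | 0.85 | 54.4 | 86% |
| 0.9 | 0.20 | 0.19 | 0.95 | 60.8 | 82% |

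The last column is a normal approximation. A simulation at 32 per arm (6,000 runs per scenario), which includes the small cost of estimating the slope, gave ANCOVA power of 92%, 88% and 84% at r = 0.3, 0.5 and 0.7, against 78% to 79% for the change-score t-test.

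**Validity.** In the same simulation with no treatment effect, two-sided type I error was 4.5% to 4.9% for the change score and 4.6% to 5.3% for ANCOVA. Both are near 5%.

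**Sensitivity to chance imbalance.** Under simple randomisation with 32 per arm, the difference in mean baseline has SD √(2/32) = 0.25 baseline SD. It exceeds 0.25 SD in either direction with probability 2 × [1 − Φ(1)] = 0.317, for each outcome taken alone. Given a baseline difference d, the expected change-score difference moves by (1 − r) × d in the opposite direction. For d = 0.25 SD:

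| r | Shift (SD) |
|---|---|
| 0.3 | 0.7 × 0.25 = 0.175 |
| 0.5 | 0.5 × 0.25 = 0.125 |
| 0.7 | 0.3 × 0.25 = 0.075 |
| 0.9 | 0.1 × 0.25 = 0.025 |

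**Scope.** These figures apply to absolute change compared by a t-test. No loss was computed for percent change or for the Wilcoxon test.

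**The case against.** The strongest reply is that nothing invalid is planned. Randomisation makes the unadjusted change-score comparison unbiased on average, and type I error holds. The gain from adjustment depends on a correlation that the document does not give. At r = 0.9 it is only 5% of the variance. Only secondary outcomes are involved. All of that stands, and it sets the weight of the point.

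Several stronger readings are tempting, but the document does not support them:

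- *All four secondary objectives are affected.* They are not. Objective 1 (operative time, transfusion, conversion to open surgery, hospital stay and similar) has no baseline value and no change score. The adverse-event part of objective 4 has none either.
- *The baseline is ignored.* It enters by subtraction, or by division for percent change. What is missing is its use as a covariate.
- *Percent change is explicitly assigned to these tests.* The test sentence in {20a} names only change from baseline. Applying it to fibroid size and uterine volume is the natural reading alongside the outcome definitions, but it is not written out.
- *The open choice between t-test and Wilcoxon is a defect.* The rule for choosing may stand in the analysis plan, which is not shown, so it is not counted here.

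It could also be said that covariate adjustment is itself detail for the analysis plan. That does not hold in this case, because the article states the between-group test for these outcomes.

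**Conclusion.** The point holds as one of efficiency and robustness. The stated comparison for hemoglobin, KKSI and UFS-QOL, and by natural reading for fibroid size and uterine volume, does not adjust for a baseline value that the trial collects. For absolute change, adjustment would cut the variance by 35% at r = 0.3, 25% at r = 0.5, 15% at r = 0.7 and 5% at r = 0.9. It would also remove a conditional shift of 0.025 to 0.175 SD for a baseline difference of 0.25 SD.

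These sizes rest on an assumed r, equal SDs, a linear relation and 32 evaluable women per arm. A reader might infer that the planned tests are biased or that the trial's main conclusion is at risk. Neither follows: the tests are valid under randomisation, and the primary noninferiority test, its margin and the enrolment of 80 are unaffected. The change is worth making because it is nearly free.

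**What to change.** In Statistical methods {20a}, and in the analysis plan, make ANCOVA the between-group comparison for hemoglobin, KKSI and UFS-QOL at each stated time point. Regress the follow-up value on treatment arm and that outcome's own baseline, using the same baseline value from which the change is measured. State that the adjustment applies whether or not an imbalance is seen.

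Do likewise for fibroid size and uterine volume, preferably as log follow-up on log baseline, with the arm difference back-transformed to a percent difference. Keep the change and percent-change summaries as descriptive results. Adding the minimisation factors, or using a repeated-measures mixed model for outcomes with several visits, is optional.

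The cost is wording only, since the baseline data are already recorded. Recruitment ended on 31 December 2023, and the analyst receives the data after database lock, so timing matters. Specify the change before lock; if lock has passed, report the adjusted results as a sensitivity analysis and label them so.

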### Interim analyses {21b}

Interim analyses will not be conducted.

### Methods for additional analyses (e.g., subgroup analyses) {20b}

Subgroup analyses will not be conducted. However, when baseline factors differ between groups and might affect the primary outcome, an analysis of covariance (ANCOVA) with the factor as a covariate will be considered.

### Methods in analysis to handle protocol non-adherence and any statistical methods to handle missing data {20c}

The Case Review Committee will discuss procedures for handling missing data. The data will be classified as missing, and no imputation method will be used.

### Plans to give access to the full protocol, participant level-data and statistical code {31c}

The complete study protocol in Japanese is available upon reasonable request to the corresponding author.

## Oversight and monitoring

### Composition of the coordinating center and trial steering committee {5d}

The chief investigator has contracted with the clinical research organization, EPS Corporation, to be the coordination center of the study. The company provides overall management, monitoring, auditing (if performed), data management, statistical analysis, and medical writing services. In addition, the CRO will periodically submit reports on their work progress and results to the chief investigator. Meetings between the chief investigator, investigators at participating institutions, and CRO representatives will be held when required.

### Composition of the data monitoring committee, its role and reporting structure {21a}

A designated monitor by the principal investigator will visit each participating hospital and verify the source document of the first registered participant and report the monitoring results to the principal investigator. Monitoring of the second and subsequent participants will be conducted as needed. Monitoring will be carried out by EPS Corporation, independently of the funder, ASKA Pharmaceutical Co., Ltd.

### Adverse event reporting and harms {22}

Any expected or unexpected AEs related to the conduct of research include abnormal laboratory values or symptoms, in addition to disease, disability, infection, or death. Expected AEs are those listed in the package inserts of test and control drugs. When possible, the relationship with the AE and test drug or procedure will be specified as one of the following: not related or due to surgery, test drug, control drug, concomitant medications, other, or unknown. The AEs categorized as unknown are those in which the incidence, frequency, and conditions of the AE are not described in package inserts of test and control drugs, research protocol, and informed consent form.

The investigator shall state in the CRF the name of the disease, date of onset, severity level, treatment details, and outcome. When an investigator becomes aware of a serious illness or other AE in the conduct of the clinical study, the investigator shall promptly report this to the supervisor (chief medical officer) of the participating medical institution and the chief investigator, who shall report this to the Certified Review Board, provide information to other investigators, and promptly report the content of such information to the administrators of the participating medical organizations. The schedule for reporting is described in the complete protocol.

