#### Safety outcome measures

AEs; adverse drug reactions; intraoperative complications; postoperative complicationsBlood pressureEndocrinology (estradiol, progesterone, luteinizing hormone, follicle-stimulating hormone)Blood chemistry (aspartate aminotransferase, alanine aminotransferase, triglycerides, total cholesterol, high-density lipoprotein cholesterol, low-density lipoprotein cholesterol)Bone mineral densityBone turnover markers (tartrate-resistant acid phosphatase-5b, bone-specific alkaline phosphatases)Menstrual status (start and end dates)Endometrial thicknessHistopathological examination of the extracted myoma, including examination for malignancy or cellular degeneration

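### The relationship category 'unknown' for adverse events is defined by whether the event is already described, which is expectedness and not causality

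*Protocol article*

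**What the plan says.** Two parts of the protocol article bear on this.

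- **Adverse event reporting and harms {22}, relationship.** The article introduces a scale: "When possible, the relationship with the AE and test drug or procedure will be specified as one of the following". The options are "not related or due to surgery, test drug, control drug, concomitant medications, other, or unknown".
- **Same section, the next sentence.** It defines the last option: "The AEs categorized as unknown are those in which the incidence, frequency, and conditions of the AE are not described in package inserts", and the sentence goes on "of test and control drugs, research protocol, and informed consent form". So three kinds of reference document are named, not the package inserts alone.
- **Same section, expectedness.** Just before the scale, this has its own definition: "Expected AEs are those listed in the package inserts of test and control drugs".
- **Same section, recording.** The AE items to be entered are given as follows: "The investigator shall state in the CRF the name of the disease, date of onset, severity level, treatment details, and outcome". Neither relationship nor expectedness is named in that list.
- **Safety outcome measures.** The list opens with "AEs; adverse drug reactions; intraoperative complications", so adverse drug reactions are an outcome separate from AEs. Safety of the treatments is also part of the fourth secondary objective (Objectives {7}).

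**The concern.** Relationship and expectedness are different attributes of an AE. Relationship is a judgement about what caused the event in this patient. Expectedness is a comparison of the event with reference documents. An event can be undescribed and clearly caused by a drug, or well described and of uncertain cause. The article puts an expectedness criterion on one category of the relationship scale, so that category no longer measures relationship.

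What is at stake is the adverse drug reaction outcome. Separating reactions from AEs in general needs a relationship rating, and this scale is the only one the article gives. The Background states that preoperative relugolix before laparoscopic myomectomy has not been studied in a randomized trial. Reactions not yet described are therefore part of the new safety information the trial could provide, and they are the events whose rating this definition disturbs. The trial is also open-label (Who will be blinded {17a}), so an ambiguous category leaves room for coding that differs between arms or hospitals.

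**Working it through.** No arithmetic applies: the point depends on no effect size, SD, margin or sample size, and the article gives no AE figure to reproduce. The check is to apply the stated definitions literally to every type of event.

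**Step 1. Cross the two attributes.** The rows are the investigator's judgement of cause. The columns say whether the event is described in the reference documents.

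| Judgement of cause | Described | Not described |
|---|---|---|
| Due to a study drug | 'test drug' or 'control drug' | 'test drug' or 'control drug', **and** 'unknown' |
| Not related, or due to another named cause | the matching category | the matching category **and** 'unknown' |
| Cannot be determined | **none**: the definition of 'unknown' is not met | 'unknown' |

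Three of the six cells have exactly one category. Two cells have two categories, although one must be chosen, and one cell has none. The opening words of the scale allow for cases where a rating is not possible, so an event in the empty cell might be left unrated. It would still not be 'unknown' as defined.

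**Step 2. Compare the two definitions that refer to documents.** An expected AE is one listed in the package inserts. An 'unknown' AE is one not described in the inserts, the research protocol and the consent form. The reference sets differ. An event described only in the protocol or consent form is not 'expected' by the first definition, and need not be 'unknown' by the second. So even if 'unknown' was meant as 'unexpected', the two sentences are not complements of each other.

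**Step 3. Follow an undescribed event attributed to a study drug into the adverse drug reaction outcome.** Two things decide where it ends up, and the article states neither: whether the definition of 'unknown' overrides attribution to a drug, and which categories count as adverse drug reactions.

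- Attribution takes precedence: the event is rated 'test drug' or 'control drug' and is counted.
- The definition takes precedence, and only 'test drug' and 'control drug' count: the event is left out.
- The definition takes precedence, and 'unknown' also counts because a relationship is not ruled out: the event stays in. Undescribed events judged unrelated, or due to surgery or another cause, also come in if they were coded 'unknown' by the same definition.

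The outcome is sound under the first reading. Under the second it loses undescribed reactions, and under the third it gains unrelated events.

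**The case against.** A reader might infer that every undescribed reaction would be dropped from the adverse drug reaction count. The article does not support that. It needs both an override rule and a counting rule, and the article contains neither. The options 'test drug' and 'control drug' carry no condition that the event be listed. The counting rule is the kind of detail a condensed article leaves to the complete protocol or the analysis plan, so its absence here is not a fault.

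There is also an innocent reading. The section opens by mentioning expected and unexpected events and defines only the first. The sentence on 'unknown' may be the missing counterpart, placed after the relationship list when the text was shortened. The working CRF may already keep the two items apart. The listed CRF items do not settle this, and no miscoded event has been shown.

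Finally, no event is lost. AEs are a separate outcome, and name, onset, severity, treatment and outcome are recorded whatever the relationship.

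All of this stands, and it limits the consequence. It does not remove the defect. The article uses the same word as a relationship category and then defines events put in that category by a criterion that is not about relationship. That is a stated definition, not an omission. The innocent reading also leaves two expectedness definitions with different reference sets.

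**Conclusion.** The point holds as a flaw in a stated definition. 'Unknown' is a category on the relationship scale but is defined by expectedness. As a result, undescribed events judged to have a known cause or to be unrelated fit two exclusive categories, and described events of undeterminable cause fit none.

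The consequence is possible misclassification of undescribed reactions. Whether they are then left out of the adverse drug reaction outcome, or mixed with unrelated events, depends on a counting rule that is not shown. The number of events cannot be estimated from the article, and no proportion should be quoted. The effect is confined to one safety outcome. The overall AE count, the primary comparison of blood loss and the sample size do not depend on it.

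This conclusion assumes that the article renders the complete protocol faithfully here. If the complete protocol already separates the two items, only the article's wording needs correcting.

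**What to change.** 1. Rate relationship and expectedness as two separate items for every AE.
2. In the relationship item, reserve 'unknown' for a relationship that cannot be determined.
3. Apply the criterion of not being described in the package inserts, protocol and consent form to expectedness only, and reconcile it with the existing definition of expected AEs so that both use the same reference set.
4. Before database lock, check the relationship rating of any event coded 'unknown' because it was unlisted, and have the investigator give a relationship rating for it.

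The cost is a change of wording in the protocol and CRF guidance and a small query round. Recruitment ended on 31 December 2023 (Trial status), but the check needs no new patient data. If the complete protocol and CRF already keep the items apart, the query round falls away and only the wording remains to be corrected.
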